**Study Protocol**

**Title: Efectos de la PEEP individualizada o estándar sobre la mecánica y eficiencia respiratoria.**

**Title: Effects of the individualized versus standard PEEP on respiratory mechanics and effiency.**

**Methods**

The study will be performed at the Department of Anesthesiology and Critical Care at the Hospital Clínico Universitario de Valencia, after the approval by the Local Ethics Committee. Written informed consent will be obtained from all patients. The recruitment of patients is planned to be of 6 months duration after the approval.

The study is designed as a randomized two parallel arm open study. Eligible subjects will be randomized 1:1 to one of the two treatment arms. For randomization a computer generated list of random numbers will be used. The participants will be assigned to the study groups by the sequential opening of numbered envelopes containing the randomization assignment. The study includes consecutive:

Inclusion criteria:

Patients with ASA physical status I-III undergoing elective pancreaticoduodenectomy and liver resection.

Exclusion criteria:

Age of <18 years, ASA more than III, laparoscopic surgery and patients with respiratory disease.

**2.4.- Sample size (n).**

The sample size needed to be included in the study was calculated by the statistical program GPower 3.1.5.

The “n” was calculated based in the primary outcome which is the behavior in driving pressure in 30 consecutives patients after individualized or standardized PEEP measured in a previous trial in patients undergoing one-lung ventilation. Based in the results of Ferrando et al (Anesth Analg 2014) Following measurements of the differences magnitude. (effects of the sample size) of 0.25^[[1]](#footnote-1)^; level of significance α = 0,05^[[2]](#footnote-2)^; power 1-β =95%^[[3]](#footnote-3)^;

[4] *-- Thursday, January 03, 204 -- 18:13:20*

**F tests -** ANOVA: Repeated measures, within factors

**Analysis:** A priori: Compute required sample size

**Input:** Effect size f = 0.32

α err prob = 0.05

Power (1-β err prob) = 0.95

Number of groups = 1

Number of measurements = 4

Corr among rep measures = 0.5

Nonsphericity correction ε = 1

**Output:** Noncentrality parameter λ = 18.0000000

Critical F = 2.6911329

Numerator df = 3.0000000

Denominator df = 105

Total sample size = 36

Actual power = 0.9519863

*General procedures*

Patients will be monitored for nasopharyngeal temperature, ECG, pulse oximetry, and invasive arterial pressure using the GE Aisys Carestation™ monitor. The depth of anesthesia will be monitored with the bispectral index (BIS vista, Aspect Medical Systems, The Netherlands), and cardiac index (CI) with the Pulsioflex monitor (Pulsion Medical System AG, Munich, Germany)

Prior to anesthesia induction, a thoracic epidural catheter (Tuhoy; Braun Laboratories, Melsungen AG, Germany) will be placed at T6 to T10, and 3 mL of bupivacaine 0.25% with epinephrine will be administered. After 5 min of breathing 0.8 oxygen, anesthesia will be induced with fentanyl 5 µg kg^-1^, propofol 2.5 mg kg^-1^, and rocuronium 0.6 mg kg^-1^. Sevoflurane will be administered to maintain a BIS between 40–50. Patients will received a continuous infusion of remifentanil 0.1–0.4 µg kg^-1^ min^-1^. Crystalloid solutions will be continuously infused at a rate of 3 ml kg^-1^ h^-1^.

The patient’s lungs will be ventilated with the GE Aisys Carestation™ using volume-controlled ventilation with square-wave flow as follow: VT of 8 ml kg^-1^ of predicted body weight (PBW), inspiratory-to-expiratory ratio of 1:2 with an end-inspiratory pause of 10%, PEEP of 5 cmH_2_O, inspiratory oxygen fraction (FiO_2_) of 0.5 and respiratory rate (RR) adjusted to maintain end-tidal CO_2_ (EtCO_2_) between 35–55 mmHg.

*Monitoring*

To monitor respiratory mechanics and efficiency the NICO monitor and the software DataColl (both Respironics, Wallingford, CT) will recorde respiratory, SpO_2_, and VCap data. Respiratory data will consisted of VT, airway and plateau pressures (Paw and Pplat), dynamic respiratory compliance (Cdyn = VT/ peak pressure − PEEP), expiratory airway resistance (Raw = peak pressure − PEEP/flow) and driving pressure (Pplat – PEEP).

The mainstream CO_2_ sensor will be zeroed and placed at the airway opening. Expired CO_2_ concentrations and VT data will be downloaded into MATLAB® (MathWorks, Natick, MA), which constructs volumetric capnograms according to the functional approximation using the Levenberg–Marquardt algorithm. We measured (1) VTCO_2_,br or tidal elimination of CO_2_ within one breath measured by integrating the area under the curve (AUC) of Vcaps, (2) the normalized VTCO_2_,br to alveolar tidal volume as follow:

VTCO_2_,br / VTalv

(3) dead space, calculated noninvasively using Bohr’s formula:

VDBohr (VD/VT) = (PACO_2_−PēCO_2_)/PACO_2_

where PACO_2_ is the mean alveolar partial pressure of CO_2_ measured at the midpoint of the alveolar plateau phase III and PēCO_2_ is the mixed expired partial pressure of CO_2_, (4) VDalv/VTalv calculated as follow:

VDalv/VTalv = (VDPhy – VDaw) = [(VDBohr/VT) x VT – VDaw] / VTalv.

*Experimental protocol*

After anesthesia stabilization, baseline data will be recorded during 10 minutes. The first 5 minutes will be considered for stabilization and the last 5 min of each VT will be analyzed. Five cmH_2_O of PEEP will be maintained during this part of the study.

Durign the next step of the protocol a recruitment maneuver will be performed as previously described^9^. At this moment patients will be randomized to continue with 5 cmH_2_O of PEEP after the RM (n = 16) or either to received an open–lung PEEP determined by a decremental PEEP titration trial (n = 16). This PEEP trial consists in a decrement in PEEP in step of 2 cmH_2_O during 2 minutes, from 20 to zero, looking for the highest dynamic compliance, which will consider as the optimal PEEP^10^. Thereafter, a new alveolar recruitment maneuver will be performed as described above to re-open alveoli collapsed during the decremental PEEP titration. The OL-PEEP (optimal PEEP) will be applied and maintained throughout the study period.

*Statistical analysis*

A total of 36 patients will be included in the study. First, the patient baseline variables will be described and the homogeneity of these groups evaluated using appropriate statistical tests for the type of variable being analyzed (mean difference of proportions, chi-square, ANOVA, with a corresponding confidence interval of 95%). The parameters will be presented as mean (± SD) or median (interquartil range). Statistical analysis will be performed using the SPSS 20.0 software package (SPSS, Chicago, IL, USA). P-values < 0,05 are considered significant.

1. 1 El efecto del tamaño de la muestra es la cuantificación de la magnitud de la diferencia. Detalla el tamaño de una diferencia (por ejemplo, entre dos valores medios) que debe considerarse como de interés, es decir, la magnitud que debe tener una diferencia para considerarla como significativa. En otras palabras, afinando con el efecto del tamaño de la muestra, podemos detectar diferencias (por ejemplo, entre dos valores medios) a nivel de décimas, o de centésimas. Cuanto más exigente sea nuestra necesidad (detectar las diferencias en las centésimas, que no en las décimas), el tamaño de la muestra será mayor. En nuestro caso, se ha optado por un efecto del tamaño de la muestra igual a 0,25; un efecto del tamaño medio, ni muy poco exigente, ni muy exigente (Quinn and Keough, 2002). [↑](#footnote-ref-1)
2. 2 El nivel de significatividad de un test se define como la probabilidad de tomar la decisión de rechazar la hipótesis nula (H_0_) cuando ésta es verdadera (decisión conocida como Error tipo I, o "falso positivo"). En nuestro caso, se ha tomado un nivel de significación estándar de 0,05 (Casella and Berger, 2002). [↑](#footnote-ref-2)
3. 3 La potencia del test mide la confianza que tenemos para poder detectar diferencias (por ejemplo entre valores medios) si es que existen. En nuestro caso, trabajamos con un 95% se confianza (Casella and Berger, 2002). [↑](#footnote-ref-3)

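### The printed airway-resistance formula includes the driving pressure, so resistance could appear to differ between arms when it does not

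*Protocol*

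**What the plan says.** The Monitoring subsection defines three derived variables in one sentence:

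- "dynamic respiratory compliance (Cdyn = VT/ peak pressure − PEEP"
- "expiratory airway resistance (Raw = peak pressure − PEEP/flow"
- "driving pressure (Pplat – PEEP"

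It lists "airway and plateau pressures (Paw and Pplat" among the recorded data. The ventilator settings just before it are "volume-controlled ventilation with square-wave flow" and "inspiratory-to-expiratory ratio of 1:2 with an end-inspiratory pause of 10" per cent, with tidal volume set at 8 ml/kg of predicted body weight and respiratory rate adjusted to end-tidal CO2.

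The sample-size section names "the primary outcome which is the behavior in driving pressure". Under Experimental protocol, PEEP in the individualized arm is the step of the decremental trial at which dynamic compliance is highest. The other arm stays at 5 cmH2O.

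**The concern.** Airway resistance is a pressure lost to flow, divided by that flow. The printed numerator also contains the elastic pressure that distends the lung and chest wall, which is the trial's primary outcome. The label says expiratory while the pressure is an inspiratory peak, and the flow is not identified.

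This matters more here than in most trials because the overlap is linked to the allocated strategy. At a given tidal volume, the PEEP with the highest dynamic compliance is the PEEP with the smallest peak-minus-PEEP difference, and that difference is the numerator of Raw. At constant flow, the titration therefore picks the lowest Raw in the individualized arm, while the control arm undergoes no such selection. The title announces effects on respiratory mechanics, so a table showing lower resistance under individualized PEEP would be read as a separate finding. It could be the driving-pressure effect carried over. A true change in resistance could also be masked.

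**Working it through.** The protocol gives no numerical value for Raw, so there is no figure to reproduce. The check is algebra on its own definitions, then illustrations under declared assumptions.

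**1. Brackets.** Read literally, peak − (PEEP/flow) mixes units and cannot be meant. The evident reading is Raw = (peak − PEEP)/flow, and likewise Cdyn = VT/(peak − PEEP).

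**2. Decomposition.** Peak − PEEP = (peak − Pplat) + (Pplat − PEEP). Dividing by inspiratory flow:

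Raw = (peak − Pplat)/flow + driving pressure/flow.

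The first term is inspiratory resistance. The second is the primary outcome, rescaled. A change of x cmH2O in driving pressure moves Raw by x/flow with resistance unchanged.

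**3. Link to compliance.** Raw = VT/(Cdyn × flow). At fixed VT and flow, Raw varies inversely with Cdyn.

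**4. Size per 1 cmH2O, if flow is inspiratory.** From the protocol: VT 8 ml/kg, I:E 1:2, pause 10%. Assumed, not in the protocol: predicted body weight 55–75 kg, rate 12–14 per minute. Inspiratory time Ti = (60/RR)/3. The protocol does not say what the 10% refers to, so both readings are shown.

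*Pause as 10% of inspiratory time:* flow = VT/(0.9 × Ti).
- 55 kg, RR 12: 0.44 L / (0.9 × 1.667 s) = 0.29 L/s; 1/flow = 3.4
- 65 kg, RR 12: 0.52 / 1.5 = 0.347 L/s; 1/flow = 2.88
- 75 kg, RR 14: 0.60 / (0.9 × 1.429) = 0.47 L/s; 1/flow = 2.1

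*Pause as 10% of the whole cycle:* flow = VT/(Ti − 0.1 × 60/RR).
- 55 kg, RR 12: 0.44 / (1.667 − 0.5) = 0.38 L/s; 1/flow = 2.7
- 75 kg, RR 14: 0.60 / (1.429 − 0.429) = 0.60 L/s; 1/flow = 1.7

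An assumed 3 cmH2O fall in driving pressure would therefore lower Raw by about 5–10 cmH2O/L/s across both readings.

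**5. Relative size, if flow is inspiratory.** Assumed: true resistance fixed at 10 cmH2O/L/s, driving pressure falling from 12 to 8 cmH2O.

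| Inspiratory flow (L/s) | Printed Raw, before → after | Change | (peak − Pplat)/flow |
|---|---|---|---|
| 0.3 | 50.0 → 36.7 | −27% | 10 → 10 |
| 0.5 | 34.0 → 26.0 | −24% | 10 → 10 |
| 0.8 | 25.0 → 20.0 | −20% | 10 → 10 |

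Driving pressure makes up 50% to 80% of the numerator across these cases.

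**6. If flow is expiratory.** Take peak expiratory flow as driving pressure/expiratory resistance, with that resistance also assumed to be 10. At 0.5 L/s inspiratory flow:
- driving pressure 12: (5 + 12)/1.2 = 14.2
- driving pressure 8: (5 + 8)/0.8 = 16.3

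Raw rises by about 15%. It still depends on driving pressure, but in the opposite direction.

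**The case against.** The strongest reply is about reach. Raw appears once, in a list of recorded variables. The protocol attaches no hypothesis or between-arm test to it, and the sample size and the primary comparison do not use it. A reader might infer that the trial will claim a PEEP effect on airway resistance. The protocol does not support that: it announces no such claim, and one can say only that the definition would allow it. Nor is the primary outcome compromised, because plateau minus PEEP is correctly defined.

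A reader might also conclude that Raw is nothing but inverted compliance, or that any Raw effect is purely a driving-pressure effect. Both go too far. The inverse relation is exact only at fixed tidal volume and flow. Tidal volume varies with predicted body weight, and rate is adjusted to CO2, so at a fixed I:E ratio flow varies too. The resistive term also remains in the formula: the measure is contaminated, not empty.

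The size and sign depend on which flow is meant, on how the 10% pause is counted and on a rate that the protocol leaves free. The range of 12–14 is only illustrative. This objection stands, and the figures are conditional.

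Finally, the monitor and its software record the respiratory data, so the value stored may be the device's own resistance and not this calculation. The protocol does not say. If so, the error is one of wording, but the printed definition still needs correcting. The missing brackets are clerical and would mislead no analyst.

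**Conclusion.** The point holds as a wrong definition of a secondary mechanics variable. If followed, the formula does not give resistance, and with inspiratory flow it adds driving pressure/flow to it. Because the same pressure difference drives PEEP selection in one arm only, a between-arm difference in Raw could appear without any change in true resistance.

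The contamination follows from the protocol's own definitions and needs no outside figure. Its size does: about 1.7–3.4 cmH2O/L/s per cmH2O of driving pressure over both pause readings, given inspiratory flow and the assumed weights and rates. With expiratory flow the direction may reverse. The correction is worth making before Raw is analysed or reported, and it has no bearing on the primary comparison.

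**What to change.** Define inspiratory airway resistance as (peak pressure − plateau pressure)/inspiratory flow, name the flow, and drop the expiratory label. Square-wave flow, the end-inspiratory pause and plateau recording are already specified, so nothing new has to be measured.

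If expiratory resistance is really intended, report the monitor-derived value and state the pressure term and flow on which it rests.

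As a clerical correction, write Cdyn as VT/(peak pressure − PEEP) in place of "Cdyn = VT/ peak pressure − PEEP".

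The cost is two formula lines. Data collection, sample size and patient management do not change.

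### The sample size counts four driving-pressure measurements per patient, but the procedures time only the pre-randomisation baseline, and the one analysis-window rule refers to tidal volumes that the protocol never varies.

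*Protocol*

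**What the plan says.** **Sample size (Protocol, section 2.4).** The primary outcome is the behaviour of driving pressure after individualised or standardised PEEP. The software output is for "ANOVA: Repeated measures, within factors", with "Number of groups = 1" and "Number of measurements = 4". It returns 36 patients and a power of 0.9519863. The input line reads "Effect size f = 0.32", while the text of the section gives 0.25 and the first footnote repeats it ("se ha optado por un efecto del tamaño de la muestra igual a 0,25").

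**Ventilation (Protocol, General procedures).** One tidal volume is set, 8 ml per kg of predicted body weight. No later step changes it.

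**Recording (Protocol, Experimental protocol).** Baseline is recorded for 10 minutes at a PEEP of 5 cmH2O. The first 5 minutes are for stabilisation, and "the last 5 min of each VT will be analyzed".

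**After baseline (same section).** A recruitment manoeuvre follows, and patients are randomised at that point. One arm continues at 5 cmH2O. The other has a decremental PEEP trial in 2-minute steps and a second manoeuvre, after which the chosen PEEP is kept for the study period. No recording time, duration or analysis window is given after allocation, and the length of the study period is not stated. The Statistical analysis section names no time point either.

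**The concern.** Two parts of the protocol do not fit together. The calculation relies on four occasions per patient, and the procedures identify one, which precedes the intervention. The sentence that should say which minutes count on each occasion is tied to a quantity that takes a single value.

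Two things are at stake. First, the timing of the primary outcome is open. Driving pressure may drift after a recruitment manoeuvre and during surgery, so the moment of measurement could affect the result. Staff know the allocation, and no post-allocation window is fixed in advance, so the protocol does not prevent the choice of a favourable time. Second, the number of measurements enters the power formula directly, so a figure of 95% cannot be checked against a schedule that does not show the occasions.

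An analysis plan may settle how a window is summarised. When each patient is measured is a bedside procedure, and the protocol has already committed to a number of occasions.

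**Working it through.** **Inputs, all from section 2.4:** N = 36, one group, m = 4 measurements, correlation ρ = 0.5, ε = 1, "α err prob = 0.05". The effect size f is 0.25 in the text and footnote and 0.32 in the printed input.

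**Formula (one-group repeated-measures ANOVA, within factor):**
- λ = f² · N · m · ε / (1 − ρ)
- df1 = (m − 1)ε; df2 = (N − 1)(m − 1)ε
- power = P(noncentral F > critical F)

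**Step 1: reproduce the printed result.** With f = 0.25, λ = 0.0625 × 36 × 4 / 0.5 = 18.0, df = 3 and 35 × 3 = 105, critical F = 2.6911 and power = 0.952. These match the printed output, and 36 is the smallest N that reaches 95%. With f = 0.32, λ = 0.1024 × 36 × 4 / 0.5 = 29.49, which does not match the printed 18. The output therefore came from f = 0.25 and m = 4, and the stated N does depend on four measurements.

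**Step 2: vary only the number of measurements, N = 36.**

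| m | df | λ, f = 0.25 | power | N for 95% | λ, f = 0.32 | power | N for 95% |
|---|---|---|---|---|---|---|---|
| 4 | 3, 105 | 18.0 | 95.2% | 36 | 29.49 | 99.7% | 23 |
| 3 | 2, 70 | 13.5 | 90.6% | 43 | 22.12 | 98.9% | 27 |
| 2 | 1, 35 | 9.0 | 83.1% | 54 | 14.75 | 96.2% | 34 |

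**Step 3: what these figures measure.** With one group, the test asks whether driving pressure changes over time in all patients pooled. It does not compare the arms.

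To illustrate the difference, *assume* 18 patients per arm and a standardised difference between arms of d = 2f. The protocol states neither the between-arm test nor this link between d and f.
- One post-allocation value, unadjusted: λ = d² × 18/2 = f² × 36, which is 2.25 at f = 0.25 and 3.69 at f = 0.32. With df 1 and 34, power is about 31% and 46%.
- Mean of three post-allocation values with ρ = 0.5: the variance is (1 + 2 × 0.5)/3 = 0.667, so λ is 3.375 and 5.53, and power is about 43% and 63%.
- The same mean adjusted for baseline: the residual variance is 0.667 − 0.5² = 0.417, so λ is 5.40 and 8.85. With df 1 and 33, power is about 62% and 82%.

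**Step 4: look for the four occasions in the procedures.**
- Baseline is one occasion, before allocation.
- The 2-minute PEEP steps cannot be the others. They occur in one arm only and serve to choose the PEEP by dynamic compliance.
- The period after the assigned PEEP is set has no stated times.
- The phrase *each VT* cannot supply occasions, because there is one tidal volume.

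**The case against.** A reader might infer that the plan, followed literally, yields no driving pressure after allocation. The protocol does not support that. Its primary outcome is described as following individualised or standardised PEEP, driving pressure is among the recorded variables, and the individualised PEEP is kept for the study period. Post-allocation measurement is plainly meant; what is missing is its timing.

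A reader might also infer that the trial falls short of 95% power because fewer than four measurements will be made. That does not follow either. The number actually planned is unknown. At the printed f = 0.32, even two measurements give 96.2% by the protocol's own formula. Only f = 0.25 reproduces the output, but the document contains both values.

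It could be argued that the intended test is the group-by-time interaction. If the same f were attached to that interaction in two groups, the power at f = 0.25 and N = 36 would be almost unchanged (95.2%, 90.6% and 83.0% for 4, 3 and 2 measurements). This is fair, but the protocol does not say so, and its calculation was run with one group.

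Two further inferences lack support. The protocol says that the monitor and its software will record data, not that recording is continuous, so it cannot be assumed that usable later data will exist at every moment. Nor does anything show that the *each VT* sentence came from another study; loose wording would explain it equally well.

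What stands is the mismatch itself: four occasions are assumed, one is timed, and the window rule has no valid referent.

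**Conclusion.** The point holds as a mismatch within the protocol that should be corrected. The primary outcome has no fixed post-randomisation occasion or window in an open trial, and the stated power rests on four occasions that the procedures do not identify.

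The consequence for power is that it is unverifiable, not that it is known to be too low. By the protocol's formula at N = 36, the range across two to four measurements is 83.1% to 95.2% at f = 0.25 and 96.2% to 99.7% at f = 0.32. These figures assume ρ = 0.5 and ε = 1 as printed, and they describe change over time in one pooled group. The between-arm figures under working depend on the added assumption d = 2f and only illustrate that the two kinds of power can differ widely.

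The conflict between the two effect sizes, the single group in the calculation, and arms of 16 + 16 = 32 against a total of 36 are separate matters. They affect the size of this point but not its existence.

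**What to change.** 1. In the window rule, replace *each VT* with *each measurement period*.
2. Have the sponsor list the measurement occasions, including those after the assigned PEEP is set. They should fall at fixed times common to both arms, each with the same last-5-minutes window. The sponsor must supply the times, because the document does not show what the four occasions were meant to be.
3. State which post-randomisation occasion or occasions define the primary driving-pressure comparison.
4. Make the number of measurements in section 2.4 match that list, and restate the power for the between-arm test that will be used, with one effect size. Listing four occasions is not enough by itself, since the printed 95% would still belong to a one-group test.

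The cost is mainly protocol wording and a recalculation. Whether the listed recordings need extra work depends on how the monitor is used, which the protocol does not say. The downside is that the restated power may be less favourable than 95%.

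### The two arms are set at 16 patients each (32), but the sample-size output and the analysis section both give 36, and nothing explains the four-patient gap.

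*Protocol*

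**What the plan says.** Methods describes two parallel arms with equal allocation: "Eligible subjects will be randomized 1:1 to one of the two treatment arms". Assignment uses a computer-generated list and numbered envelopes.

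Section 2.4 bases the number of patients on a program run of the type "ANOVA: Repeated measures, within factors", with one group, four measurements, correlation 0.5, alpha 0.05 and target power 0.95. It ends with "Total sample size = 36" and an actual power of 0.9519863. The narrative gives the effect size as "effects of the sample size) of 0.25", and footnote 1 repeats that value. The input line of the program sheet shows f = 0.32.

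The Experimental protocol gives the arm sizes. For standard PEEP: "patients will be randomized to continue with 5 cmH_2_O of PEEP after the RM (n = 16". For the individualised arm: "open–lung PEEP determined by a decremental PEEP titration trial (n = 16". The Statistical analysis paragraph, which follows directly, returns to the larger figure: "A total of 36 patients will be included in the study".

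**The concern.** Two arms of 16 make 32, not 36. The total of 36 is the uninflated result of the power calculation, so the extra four cannot be read as a margin for losses, and the protocol does not describe them as one. With two arms and a 1:1 ratio there is no third group or unequal split to absorb them.

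The practical consequence is that the randomisation list and the envelopes need one length, and the protocol supports two. The statistical consequence is that a trial run at the stated arm sizes would be smaller than the protocol's own calculation requires for its stated power.

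**Working it through.** **Inputs (section 2.4).** m = 4 measurements, ρ = 0.5, ε = 1, k = 1 group, α = 0.05. Effect size f = 0.25 (narrative and footnote 1) or f = 0.32 (program input line). N = 36 (section 2.4 and Statistical analysis) or 16 + 16 = 32 (Experimental protocol).

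**Formulas, within-factor test.** λ = f² · N · m · ε / (1 − ρ); df1 = (m − 1)ε; df2 = (N − k)(m − 1)ε. Power is the probability that a noncentral F with these parameters exceeds the central F critical value.

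**Step 1: reproduce the printed output.** With f = 0.25 and N = 36, λ = 0.0625 × 36 × 4 / 0.5 = 18.0, df = 3 and 35 × 3 = 105, critical F = 2.69113, power = 0.95199. Every printed output figure is matched.

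**Step 2: try the printed input.** With f = 0.32 and N = 36, λ = 0.1024 × 36 × 4 / 0.5 = 29.5 and power = 0.997. With that effect size, 23 patients would reach 0.95. So f = 0.32 does not produce the printed λ of 18, total of 36 or power of 0.952.

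**Step 3: use the arm sizes as written.** With f = 0.25 and N = 32, λ = 0.0625 × 32 × 4 / 0.5 = 16.0, df = 3 and 31 × 3 = 93, critical F = 2.7025.

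| N | Power (f = 0.25, one-group within-factor) |
|---|---|
| 32 | 0.923 |
| 33 | 0.932 |
| 34 | 0.939 |
| 35 | 0.946 |
| 36 | 0.952 |

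The smallest N that reaches 0.95 is 36. At 32 the type II error is 1 − 0.923 = 7.7%, against 1 − 0.952 = 4.8% at 36.

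**Step 4: sensitivity to f.** With f = 0.32 and N = 32, λ = 0.1024 × 32 × 4 / 0.5 = 26.2 and power = 0.994.

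**Step 5: what the 95% covers.** The run has one group and so contains no comparison of arms. Two two-arm tests with the other inputs unchanged show how far the figure carries over.

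- *Group-by-time interaction* (same λ, df2 = (N − 2) × 3): power 0.952 at 36 and 0.923 at 32 for f = 0.25.
- *Between-arm main effect*, λ = f² · N · m / (1 + (m − 1)ρ), df = 1 and N − 2. At 36, λ = 0.0625 × 36 × 4 / 2.5 = 3.6, critical F = 4.130, power = 0.454. At 32, λ = 0.0625 × 32 × 4 / 2.5 = 3.2, critical F = 4.171, power = 0.410.

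**The case against.** **The shortfall vanishes at f = 0.32.** This is correct arithmetic: 32 patients would then give 99.4%. But that value cannot have generated the printed output, whereas the narrative, footnote 1 and λ = 18 all agree on 0.25. What stands is that the power loss must be stated as conditional on f = 0.25. The conflict between 32 and 36 exists under either value.

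**The total is stated twice as 36, and 32 is only implied by the arm sizes.** This is also fair, and it makes 36 the likelier intention. The arm sizes are still explicit and still do not add up to it.

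**Perhaps 36 are included and 32 randomised, since randomisation follows baseline recording.** The protocol does not say so. Even if it did, 32 would be below the 36 that the calculation requires.

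**The consequence is small.** On the protocol's own calculation the loss is about 3 percentage points, and for a between-arm main effect about 4. Neither decides whether the trial can answer its question. This objection stands and limits the severity.

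**A reader might infer data-dependent stopping.** Because the trial is open, one could suspect that two totals let the team stop at 32 or continue to 36 according to the results. The protocol describes no interim look and no outcome-based stopping, and an open design does not by itself mean that accruing results are reviewed. The documents do not support that inference.

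**Conclusion.** The contradiction is real and unexplained: 32 patients by the arm sizes, 36 by the sample-size output and the analysis section. Under the calculation that reproduces the printed output, running the trial at 32 lowers power from 95.2% to 92.3%. That figure rests on f = 0.25, four measurements, correlation 0.5, sphericity and the one-group within-factor test.

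A reader might conclude that the randomised comparison has 95% power at 36 and loses it at 32. The protocol does not support this, because the 95% belongs to a test with no arm comparison in it. It would carry over to a group-by-time interaction with the same f, but the protocol does not name that as the primary test. For a between-arm main effect at f = 0.25, power is about 45% at 36 and 41% at 32, so choosing 36 restores the protocol's own calculation without powering that contrast.

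Severity is moderate. The strongest reason to correct it is that the randomisation list and envelopes need a single number.

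**What to change.** Change both arm sizes in the Experimental protocol from 16 to 18, so that they sum to the 36 already planned, and build the randomisation list and the numbered envelopes for 36. This costs two numbers in the text and no enrolment beyond the stated total.

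If only 32 patients will be randomised, state 32 throughout and give the power of the protocol's own calculation as about 92%, explicitly for f = 0.25 and the one-group within-factor test. Quoted without those conditions, 92% would be misread as the power of the two-arm comparison.

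In either case, reconcile the effect size in section 2.4. The printed f = 0.32 should be corrected to the 0.25 that yields the printed output. If 0.32 was truly intended, the calculation must be rerun, because 36 does not follow from it.

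### Driving pressure is measured before randomisation, but baseline is assigned only description and homogeneity tests; adjusting the arm comparison for it would gain precision for one degree of freedom

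*Protocol*

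**What the plan says.** **Baseline measurement.** The Experimental protocol section states: "After anesthesia stabilization, baseline data will be recorded during 10 minutes". It keeps PEEP at 5 cmH2O in everyone during this part and analyses the last five minutes. General procedures sets tidal volume at 8 ml/kg predicted body weight for all patients. Monitoring lists driving pressure among the recorded respiratory data. Randomisation follows, at the recruitment manoeuvre.

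**Stated use of baseline.** The Statistical analysis section has baseline variables described and "the homogeneity of these groups evaluated using appropriate statistical tests for the type of variable being analyzed". It then covers summary statistics, software and the significance threshold. It names no between-arm test, model or covariate for driving pressure.

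**The only model named for the primary outcome.** Section 2.4 (Sample size) uses "ANOVA: Repeated measures, within factors" with "Number of groups = 1", four measurements and a correlation of 0.5 among them. It does not say which time points the four measurements are.

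**The concern.** Arms are allocated 1:1 at random, so any baseline difference between them is due to chance. A significance test asks whether chance produced it, and the answer is already known. A non-significant result does not show that an imbalance is harmless either: with 16 to 18 patients per arm, a sizeable one passes unnoticed and carries over into an unadjusted comparison.

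The design also supplies a pre-randomisation value of the primary outcome itself, taken under a common PEEP and a common tidal-volume rule. In a trial this small, leaving that value out of the arm comparison gives up precision that costs no patient and no extra measurement. It also leaves the choice of adjustment open until the homogeneity tests have been seen.

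**Working it through.** **1. The plan's own figure.** Inputs from section 2.4: N = 36, m = 4 measurements, ρ = 0.5, ε = 1, "α err prob = 0.05", "Power (1-β err prob) = 0.95".

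λ = f²·N·m·ε/(1 − ρ). With f = 0.25: 0.0625 × 36 × 4 / 0.5 = 18.0. The degrees of freedom are 3 and 35 × 3 = 105, critical F is 2.691 and power is 0.952. This matches the printed output exactly. The printed input "Effect size f = 0.32" does not: λ = 0.1024 × 36 × 4 / 0.5 = 29.49 and power is 0.997. That is a separate inconsistency. What matters here is that the 95% belongs to a time effect in one group and says nothing about the arm comparison.

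**2. What a homogeneity test can miss.** With 18 per arm, the standard error of a baseline difference is √(2/18) = 0.333 SD. On 34 degrees of freedom (critical t 2.03) it reaches significance only beyond 2.03 × 0.333 = 0.68 SD. With a baseline-outcome correlation of 0.5, an imbalance just below that moves the unadjusted post-randomisation difference by about 0.5 × 0.68 = 0.34 SD.

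**3. Variance after adjustment, one post-randomisation value.** The residual variance is (1 − ρ²) of the unadjusted variance, and the gain in effective sample size is 1/(1 − ρ²) − 1.

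| Assumed ρ | Variance factor | Gain in effective N |
|---|---|---|
| 0.3 | 0.91 | 10% |
| 0.5 | 0.75 | 33% (36 act like 48) |
| 0.7 | 0.51 | 96% |

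**4. Three post-randomisation values averaged, compound symmetry.** The variance of the mean is (1 + 2ρ)/3, and baseline removes ρ².

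- ρ = 0.5: 0.667 − 0.25 = 0.417. The ratio is 0.625, a fall of 37.5%. The gain is 1/0.625 − 1 = 60%.
- ρ = 0.3: 0.533 − 0.09 = 0.443. The ratio is 0.831 and the gain about 20%.
- ρ = 0.7: 0.80 − 0.49 = 0.31. The ratio is 0.3875 and the gain 158%.

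**5. What this does to power.** The protocol gives no between-arm difference or SD, so the standardised differences d are assumptions. Noncentral t, two-sided 0.05, 18 per arm, ρ = 0.5, one degree of freedom lost to the covariate:

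| d | One value: unadjusted → ANCOVA | Mean of three: unadjusted → ANCOVA |
|---|---|---|
| 0.5 | 30.8% → 39.1% | 43.1% → 61.6% |
| 0.64 | 46.3% → 57.6% | 62.7% → 82.3% |
| 0.8 | 64.5% → 76.7% | 81.5% → 95.0% |

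With one value and ρ = 0.5, the largest gain over all d is 27% in relative terms, or 12.3 percentage points. With 16 per arm, as the Experimental protocol section has it, power at d = 0.8 goes from 59.1% to 71.4%.

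**6. Change from baseline as the alternative.** With one post value, the change score has variance 2(1 − ρ). At ρ = 0.5 that is 1.0, no better than ignoring baseline. The ANCOVA variance as a fraction of the change-score variance is 0.65, 0.75 and 0.85 at ρ = 0.3, 0.5 and 0.7.

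**The case against.** **Covariate adjustment is commonly left to an SAP, and an SAP may exist.** This is true, and the absence of an ANCOVA alone would not be a point. But the protocol does commit itself to between-group homogeneity tests, and the one outcome model it names cannot compare the arms. Both are stated choices for which a better one is available.

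**The inputs are thin.** This stands. The 0.5 is an unsourced planning value for the correlation among repeated measures, not an observed correlation between baseline and later driving pressure. The four time points are undefined, so one baseline plus three post-randomisation values is a guess. The effect sizes are assumed. Tidal volume is common per kilogram of predicted body weight, not in millilitres, and the mention of several tidal volumes in the baseline paragraph is unclear.

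A reader might also infer three stronger things that the protocol does not support.

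- *That adjustment raises power by a third or more.* The one third is effective sample size at ρ = 0.5 with one value; power there never rises by more than 27% in relative terms. With three values the relative gain is 43% at d = 0.5 (61.6/43.1) but only 17% at d = 0.8 (95.0/81.5).
- *That baseline has no part in any outcome analysis.* The four undefined measurements may include it. Only the Statistical analysis section's silence is established.
- *That the planned ANOVA dilutes the arm effect by counting baseline as an outcome level.* The protocol states no two-arm model, so there is no arm effect in it to dilute.

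**Conclusion.** The point holds as an inexpensive improvement in precision. It does not show that the planned comparison would be invalid. A pre-randomisation measurement of the primary outcome is available under common settings, the stated use of it is description plus uninformative tests, and the named model has neither an arm term nor a baseline covariate.

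On the assumption that ρ = 0.5 is the baseline-outcome correlation, adjustment is worth about one third more patients with one post-randomisation value. It is worth about 60% more with three averaged under compound symmetry. The one-value gain is sensitive to ρ: about 10% at 0.3 and about 96% at 0.7. No single power gain can be quoted, because the effect size, the number of windows and ρ are not fixed for the arm comparison.

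**What to change.** - Remove the homogeneity tests and describe baseline variables by arm.
- Name as primary analysis an ANCOVA of post-randomisation driving pressure on arm and baseline driving pressure, or a mixed model on the post-randomisation values with the same covariate. Report the adjusted difference in cmH2O with its 95% confidence interval.
- Say which of the four measurements is baseline and which post-randomisation window or windows form the outcome.
- Fix the covariate before outcome data are seen, so that adjustment does not depend on a baseline test.
- If an SAP already specifies this, bring the protocol's Statistical analysis section into line with it.

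The cost is a few sentences and one degree of freedom. No patient, measurement or procedure is added.
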